### 1.1 “Psychiatric advance directives”

“Psychiatric advance directives” specify certain aspects of treatment that the person wishes (53). A physician can confirm in writing that the person had full capacity of discernment at the time it was written. When a facilitator can be present, 61% of people write the document, versus 3% with no facilitator(54).

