## VI. Methodology

### A. *Quantitative part of research*

#### 1. Experimental design diagram

The trial is multicenter, prospective, experimental, comparative and randomized. It will have two groups of subjects:

- benefiting from the PAD program (Experimental Intervention);
- benefiting from "usual care".

Strategies are detailed in § IV. A. and IV. B. Persons who met inclusion criteria (see § V.A.) are randomly split into two groups from a list drawn up prior to the start of inclusion.

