## ***C. Number of subjects necessary and feasibility***

### **1. Number of subjects necessary**

Subjects included in the trial are people who were involuntarily admitted to hospital within the previous 12 months. According to data in French literature, the rate of involuntary hospital admission for patients suffering from psychotic disorders is 42.6% within 12 months after their previous admission(27).

Reducing these involuntary admissions by one third, i.e. 33%, would be a very significant reduction in terms of efficiency. This is a realistic hypothesis in the light of the most recent meta-analyses (59). We consider that 10% of participants will not reach experimental intervention and we estimate a 30% size effect. With these hypotheses, for an alpha risk of 2.5% (one-sided test) and 80% power, 182 subjects per group would be necessary. Over a 12-month period rate of lost to follow-up equal to 10% has been considered acceptable by the investigators involved in this project, especially with regards to the means scheduled to limit the number of people lost from sight.

Accordingly, the total number of subjects to include is 400 patients.

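### The 182 per group in VI.C.1 does not give 80% power for the stated 30% reduction: about 221 are needed, and 400 randomised gives about 71.5% to 76% power

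*Combined protocol and SAP*

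**What the plan says.** The calculation is in VI.C.1 (Number of subjects necessary) and has five steps.

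- Control rate: "the rate of involuntary hospital admission for patients suffering from psychotic disorders is 42.6% within 12 months after their previous admission".
- Target: "Reducing these involuntary admissions by one third, i.e. 33%, would be a very significant reduction in terms of efficiency".
- Allowance for non-receipt, and the resulting effect: "We consider that 10% of participants will not reach experimental intervention and we estimate a 30% size effect".
- Result: "With these hypotheses, for an alpha risk of 2.5% (one-sided test) and 80% power, 182 subjects per group would be necessary".
- Attrition and total: "Over a 12-month period rate of lost to follow-up equal to 10% has been considered acceptable by the investigators involved in this project", and then "Accordingly, the total number of subjects to include is 400 patients".

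The SAP (VI.E.2.1, Primary Outcome Measures) analyses the primary outcome by intention to treat, with an unadjusted chi-square or Fisher's exact test of two proportions. No formula or software is given for the sample size.

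**The concern.** The text moves from a 33% reduction to a 30% reduction because a tenth of participants will not get the intervention. Under intention to treat, the reduced figure is the one the primary test has to detect. The per-group number is then said to follow from these hypotheses, yet it is the size one would expect for the larger effect. The only later inflation, from 182 per group to 400 in total, is explained by loss to follow-up, so it cannot also cover the participants not reached.

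At stake is the power claimed for the primary outcome. If the trial is non-significant, readers will judge that result against a stated 20% chance of missing the planned effect. If the true chance is higher, a null result will look like stronger evidence against the intervention than it is.

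**Working it through.** **Inputs**

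- Control proportion p1 = 0.426 (VI.C.1).
- Stated effect: 30% relative reduction, so p2 = 0.426 × 0.70 = 0.2982. This agrees with the dilution described: one third × 0.9 = 30.0%, and 33% × 0.9 = 29.7%.
- Undiluted effect: 33%, so p2 = 0.426 × 0.67 = 0.2854.
- One-sided alpha 0.025 (z = 1.960) and power 0.80 (z = 0.842) (VI.C.1).
- Allocation 1:1. This is an assumption: VI.A.1 says only that patients "are randomly split into two groups from a list drawn up prior to the start of inclusion", but the sample size is given per group and no other ratio appears.
- Evaluable per group: 182 as stated; 400 × 0.9 / 2 = 180 if 10% of outcomes are lost; 200 if none are lost.

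**Formula** (two proportions, pooled variance under the null, m = mean of p1 and p2)

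n = [1.960 × √(2m(1−m)) + 0.842 × √(p1(1−p1) + p2(1−p2))]² / (p1−p2)²

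**Trying to reproduce 182 with the stated 30% effect**

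m = 0.3621 and p1 − p2 = 0.1278. The two terms are 1.960 × 0.6797 = 1.332 and 0.842 × 0.6736 = 0.567, so n = (1.899)² / 0.01633 = 220.8, or 221 per group. The choice of formula does not close the gap: unpooled gives 219, arcsine 221 and continuity-corrected 237. Using 29.7% in place of 30% gives 226.

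**With the undiluted 33% effect**

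m = 0.3557 and p1 − p2 = 0.1406. The two terms are 1.327 and 0.564, so n = (1.891)² / 0.01976 = 180.9, or 181 per group. An exact one-third reduction gives 178. Solving backwards, 182 per group is the number for a 32.9% reduction.

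**Other routes to 182**

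- One-sided alpha 5% gives 174 for a 30% effect and 178 for 29.7%. Both contradict the stated 2.5%.
- Two-sided 2.5% gives 268 for the 30% effect.
- Reading the 30% as a standardised effect of 0.30 gives about 175.

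No reading at the stated alpha gives 182 for a 30% reduction.

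**Power at the planned size**

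Power = Φ{[√n × (p1−p2) − 1.960 × √(2m(1−m))] / √(p1(1−p1) + p2(1−p2))}

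For n = 182 and the 30% effect: (13.491 × 0.1278 − 1.332) / 0.6736 = 0.582, and Φ(0.582) = 0.720.

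| Evaluable per group | Power, 30% reduction | Power, 33% reduction |
|---|---|---|
| 180 (400 less 10%) | 71.5% | 79.8% |
| 182 (as stated) | 72.0% | 80.2% |
| 200 (all outcomes known) | 76.0% | 83.8% |

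Exact enumeration of the chi-square test for the 30% effect agrees: 71.9%, 72.2% and 76.2%. Fisher's exact test, which the SAP also allows, gives 68.2%, 68.5% and 73.0%.

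**The case against.** The strongest reply concerns the size of the shortfall. A single figure of about 72% treats every patient lost to follow-up as a missing primary outcome. The documents point the other way. VI.A.2.1 collects involuntary admissions from the patient and the referring psychiatrist and crosses them with PMSI data, so a missed interview need not mean an unknown outcome. The primary analysis is by intention to treat, and VI.E.6 provides for multiple imputation. This stands: the supported statement is a range, with 76.0% as the end where all 400 outcomes are known. It does not rescue the claim, because 76.0% is still below 80%.

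A reader might go further on four matters, and the documents do not carry them.

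- **That the dilution was provably left out.** No formula is shown. The match with 33% is close, but it remains an inference.
- **That the 10% not reached contradicts the 61% completion rate in I.E.1.1.** That rate is the share who wrote a document with a facilitator in a cited outside study. VI.C.1 refers to not reaching the intervention, which is a different event in a different programme, so a power figure built on 61% uptake would import an assumption the plan never made.
- **That the 30% should be diluted again to 27%.** Since 33% × 0.9 = 29.7%, the natural reading is that 30% already includes the dilution.
- **That the attrition step is a second error.** Dividing 364 by 0.9 gives 404.4 against the 400 planned. The difference between 182 and 180 evaluable per group is half a point of power.

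It can also be said that the primary test, its type I error and the estimate are untouched. That is true. The fault lies in the stated power alone.

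**Conclusion.** The point holds. On the plan's own inputs, the 30% reduction needs about 221 per group, and 182 is 39 short (about 18% below the requirement). With 400 randomised, power for that effect runs from 71.5% to 76.0%, so the chance of missing it is 24% to 28.5%, not 20%. The same 400 do give about 80% to 84% power for an overall 33% reduction, which is the effect that 182 is consistent with.

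This rests on 1:1 allocation, the 42.6% control rate, the 30% being a relative reduction that already allows for non-receipt, and the chi-square test. Fisher's test would lower each power for the 30% effect by about 3 to 4 points. The position within the range depends on how many primary outcomes are ascertained, which the plan does not quantify beyond its 10% loss figure. The top of the range requires outcomes actually observed, for example through PMSI; imputation alone should not be credited with restoring full information.

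**What to change.** Leave enrolment at 400 and reword VI.C.1. The revised text should:

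- state that 400 randomised gives about 80% power (180 evaluable per group) to 84% power (200 per group) for an overall 33% reduction, 42.6% to 28.5%, at one-sided 2.5%;
- state that for the 30% reduction after allowing for 10% not reached, 42.6% to 29.8%, power is about 71.5% to 76% over the same range of ascertained outcomes;
- remove the claim that 182 per group gives 80% power for the 30% effect, and name the formula used.

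The cost is a few sentences and a less favourable stated power. The patients, the test and the analysis do not change. For scale, holding 80% power for the 30% effect with 10% of outcomes lost would take 221 / 0.9 = 245.6, so 246 per group or 492 in total. That enlargement is not proposed here.

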### **2. Feasibility – Trial duration**

#### **2.1. Scaling up**

Inclusions will be progressive as the patients present inclusion criteria (open trial), and as the peer-worker and interviewer are able to meet new people.

Recruitment of patients will be progressive, until reaching 150 people per site for the Lyon and Marseille sites, 100 people for the Paris site, over an estimated period of 12 months. For each subject the duration of follow-up is fixed at 12 months. In total, this trial will have a duration of 30 months including 6 months of analysis.

#### **2.2. Recruitment**

Estimated inclusion rate is 8 to 9 patients per months for the Paris site, and 12 to 13 patients per month for the Marseille and Lyon sites. These estimates are considered to be realistic regarding the active file of the interviewers involved on the different sites. They have been used as the basis to calculate the workload of peer-workers and were used when drafting the budget for research operation.

#### **2.3. Strategy to limit the number of patients lost to follow-up in the “usual care” group**

Several methods are used to limit patients lost to follow-up.

- The investigators are in charge of recruiting patients from their active file. These patients are correctly followed.
- A systematical questionnaire will give several means of contacting the person: landline and cell phone numbers, address, e-mail address, facebook... If the person agrees, the interviewer can also take down contact details of family or friends, in case of loss or change of cell phone, or a change of address for example. This information will be updated at every meeting.
- Finally, the interviewers have the task of creating a relationship based on confidence, knowledge and recognition which will strengthen this link over the months of survey. If necessary, and upon the interviewer's assessment, with the person's consent, appointments will be made for physical informal meetings between survey meetings, to strengthen the link.

In case of non reply, the psychiatrist and the support team will be mobilized.

The interviewers will be careful not to be too insistent, so as not to persecute patients.

Each case will be discussed in the light of ongoing respect for the person.

## ***D. Data processing***

### **1. Data sources**

All data are recorded from an electronic case report form (eCRF) specifically elaborated for the study (eCRF CleanWEB, Telemedicine Technologies S.A.S., [www.tentelemed.com](http://www.tentelemed.com), 2015) and recorded at four specific study's times as follows: baseline assessment (T1), at 6 months (T2), and at 12 months after inclusion (T3). All assessments are based either on medical database and face-to-face questionnaires

### **2. Data quality control**

The e-CRF will be set up to allow real-time performance of the main consistency controls.

### **3. Data entry**

All data will be entered into the e-CRF on a secure laptop provided to the interviewer. These data will be entered from data sources kept by the psychiatrist (clinical data, assessments, scores...). Consistency controls will be carried out in real-time. Questionnaires will be filled in directly with the patient.

## ***E. Statistical Plan Analysis (SAP)***

This plan was prepared by [name] and [name] and validated with the research team on 15 January 2019. There were no changes in this SAP during the study.

### **1. Analysis Populations**

The inclusion criteria are as follows: being over 18 years of age; having a diagnosis of schizophrenia or bipolar I disorder or schizoaffective disorders according to Diagnostic and Statistical Manual of Mental Disorders, fifth edition (DSM-V) criteria; having been compulsory hospitalized within the past 12 months; having decision-making capacity assessed by psychiatrist in the four component abilities of a decisional capacity standard: understanding, appreciation, reasoning, and choice, from the MacArthur Competence Assessment Tool for Clinical Research (MacCAT-CR); being covered by French government health insurance; and speaking French. Exclusion criteria include the following: being considered unable to provide informed consent and being under guardianship.

### **2. Effectiveness Analysis**

#### **2.1. Primary Outcome Measures**

The analyses of the primary and secondary criteria will be performed on the intent-to-treat population. In addition, complementary per protocol analyses will be performed (that is comparison of persons who completed the intervention originally allocated).

The primary data will be summarized using frequencies. Comparisons between the two groups will be performed using chi-square or Fisher's exact tests for proportions. Multivariate analyses will be performed for the rate of admission using logistic regression. No adjustment will be carried out in the primary analysis.

Statistical analyses will be performed using SPSS Statistics for Windows, Version 20.0 (SPSS Inc. Chicago, IL, USA) or STATA 16 (StataCorp. 2019. Stata Statistical Software: Release 16. College Station, TX: StataCorp) LLC.

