## IV. Care strategies under study

### A. *Pw-PAD intervention*

#### 1. Description of the contents and procedure

A person included in the pw-PAD group is incited to fill in the DaiP document "Psychiatric Advance Directives", of which they are immediately given a copy. This document is provided in Annex 5. The person is incited to meet a peer-worker to help them to write it. A peer-worker is called immediately to quickly arrange a meeting, at a place the person has chosen, preferentially in town, outside the hospital.

The person can decide to fill out the document without the help offered.

The person is encouraged to share the filled-in document: with their healthcare agent, as well as with their referring psychiatrist, study investigator, and to give them a copy. A consultation concerning the sharing of this document will be proposed and organized by the peer-worker.

In case of psychiatric hospital admission, the patient hands the document "Psychiatric Advance Directives" to the hospital team, their healthcare agent or referring psychiatrist, so as to influence the therapy given.

PAD incite to follow the preference and choices of the people in question, but the carers are not legally bound to provide the care requested if it does not correspond to practice standards.

PAD do not have any binding value for relatives and carers.

Following inclusion, if the person chooses not to benefit from the intervention, they will be recontacted by the interviewer by phone, taking care not to be too insistent so as not to compromise any future participation. The reminder can be given by the psychiatrist at their next consultation, where the document will be given again, and the peer-worker will again be contacted if the person would like help filling it in.

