## ***B. Usual care***

### **1. Description of contents, frequency and process**

The contents, frequency and process of consultations with the psychiatrist remain the same.

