### **b. Institutional and procedural criteria**

Indicators of institutions and procedures will be systematically collected and will concern human resources, institutional resources, the actual number of directives filled in, the number of people who had recourse to a peer-worker, the number of contacts with the peer-worker required to fill in the document, the number of shared directives and with which actor(s), use of the document in case of hospitalization, anticipated directives respected or not in the case of hospitalization, the number and type of collaborative link with local partners, description of the actions performed by the peer-worker, etc. Identification of future dysfunctions, their origins and the corrective measures applied.

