## 2. Risks and constraints

On an individual level, the risks for patients who are “beneficiaries of usual care” of participating in the trial are low. There can be a feeling of losing a chance when they are told they are in the control group, double-blinding being impossible. However there is no change in their usual care pathway, and the patients will not be prevented from drafting advance directives if they take their own initiative to do so. The constraints are related to the fact that they have to go to meetings scheduled with the interviewer.

The individual risks and constraints of the patients who are “beneficiaries of the experimental program” are related to the introspection necessary for the drafting, which can cause a painful evocation of the past, related to previous episodes of coercion; there is also the meeting with the peer-worker, who is an atypical professional, which could destabilize some patients depending on the representations and potential expectations that they may have concerning this meeting.

Another constraint is related to answering the survey questionnaires according to a calendar defined in advance with the interviewer.

On an individual level, a risk related to the use of psychiatric nosology at the time of inclusion for both groups of patients, the use of the stated illnesses can be painful for certain patients who are in denial of their disorders. This is a lesser risk in the experimental arm because of the presence of the peer-worker, who has an impact on destigmatization.

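### The complementary per-protocol analysis sets self-selected PAD completers against controls who have nothing to complete; a complier-average effect would answer the same question and keep the randomisation

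*Combined protocol and SAP*

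**What the plan says.** Under Primary Outcome Measures (VI.E.2.1) the SAP makes intention-to-treat the main analysis: "The analyses of the primary and secondary criteria will be performed on the intent-to-treat population". It then adds that "complementary per protocol analyses will be performed (that is comparison of persons who completed the intervention originally allocated"). Completion is not defined for either arm. The Sensitivity Analyses section offers adjusted regressions, but does not tie them to the per-protocol comparison or to selection into completion.

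Other sections show what completion would mean:

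- **PAD arm (IV.A.1).** Taking up the offer is voluntary. The protocol provides that "if the person chooses not to benefit from the intervention, they will be recontacted by the interviewer by phone", and a participant may also write the document without the peer-worker.
- **Usual care (IV.B.1).** "The contents, frequency and process of consultations with the psychiatrist remain the same".
- **Crossover (IX.A.2).** Among controls, "the patients will not be prevented from drafting advance directives if they take their own initiative to do so".
- **Uptake data (VI.A.2.2.b).** The process indicators include "the actual number of directives filled in, the number of people who had recourse to a peer-worker". The schedule in VI.A.3, stated to cover both groups, lists process indicators at baseline, 6 and 12 months.

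**The concern.** A per-protocol comparison is fair only if the people kept in each arm would have had similar outcomes without the intervention. Here the filter acts mainly on one side. Participants who decline or never finish leave the PAD arm, and no matching group of would-be decliners leaves the control arm. If those who write a directive are steadier or more engaged, they would have had fewer involuntary admissions anyway, and the analysis credits the directive with that difference. The protocol gives some reason to expect selection: its section on risks and constraints (IX.A.2) says that drafting can revive painful memories and that meeting a peer-worker could unsettle some patients.

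What is at stake is the secondary question of whether the directive works in those who use it. The main trial result is not at stake.

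**Working it through.** **Inputs**

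- From VI.C.1: control 12-month risk p = 42.6%; one-third reduction, taken as 30% after 10% do not reach the intervention; one-sided 2.5%; 80% power; 182 per group; 400 in total.
- Uptake u, from three places: 90% (VI.C.1); about 75% (VIII.D.2 expects 50 completed documents per city, so 3 × 50 = 150 of 400/2 = 200); 61% (background literature in I.E.1.1: "When a facilitator can be present, 61% of people write the document, versus 3% with no facilitator").
- k, completers' risk divided by non-completers' risk in the absence of any effect. The documents do not give it. Assumed range: 0.6 to 0.9.

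**The plan's own figure.** A two-proportion calculation (pooled variance, no continuity correction) for 42.6% against 42.6 × 0.67 = 28.5% gives 181 per group, against 182 stated. That uses the undiluted 33% effect; the stated 30% effect (42.6 × 0.70 = 29.8%) needs 221 per group. The yardstick below is the stated diluted effect, 42.6 − 29.8 = 12.8 points.

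**Per-protocol comparison under no effect.** The PAD arm as a whole then has risk p:

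u·r_c + (1 − u)·r_n = p, with r_c = k·r_n

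So r_n = p / (u·k + 1 − u), and the spurious reduction is p − k·r_n, taking all controls as retained.

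Example at u = 0.90 and k = 0.7: r_n = 42.6 / (0.63 + 0.10) = 58.4%; r_c = 40.8%; spurious reduction 1.8 points.

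| Uptake | k = 0.6 | k = 0.7 | k = 0.9 | k = 1 |
|---|---|---|---|---|
| 90% | 2.7 | 1.8 | 0.5 | 0 |
| about 75% | 6.1 | 4.1 | 1.2 | 0 |
| 61% | 8.8 | 6.1 | 1.8 | 0 |

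(percentage points; for k above 1 the sign reverses)

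**False-positive rate.** One-sided test at 2.5%, 182 per arm before exclusions, no true effect:

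| Uptake | non-completers at 1.25 times completers' risk (k = 0.8) | 1.5 times (k = 0.67) |
|---|---|---|
| 90% | 3.9% | 5.7% |
| about 75% | 6.5% | 13.3% |
| 61% | 9.2% | 21.5% |

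Simulation (20,000 trials) agrees: 13.8% at 75% and 21.1% at 61%, both at 1.5 times.

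**Complier-average effect.** CACE = intention-to-treat risk difference / (uptake in PAD arm − uptake in controls). Its test of no effect is the intention-to-treat test. In the same simulations that test rejected in 2.3% to 2.7% of null trials, and the mean CACE lay within 0.1 point of zero. At the planned effect with no control uptake:

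- 12.78 / 0.90 = 14.2 points, one third of 42.6%, which is the undiluted effect the sample-size section starts from;
- 12.78 / 0.75 = 17.0 points;
- 12.78 / 0.61 = 21.0 points.

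With 3% uptake in controls, 12.78 / 0.87 = 14.7 points and 12.78 / 0.58 = 22.0 points.

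The intention-to-treat standard error at 182 per arm is √(0.426 × 0.574/182 + 0.298 × 0.702/182) = 5.0 points. Dividing by uptake, treated as known, gives 5.5, 6.7 and 8.2 points at 90%, 75% and 61%.

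**The case against.** - **The main inference is safe.** Intention-to-treat governs the primary and secondary criteria, and a per-protocol table beside it is a common layout. This stands. A reader might infer that the trial's conclusion is tilted towards the intervention; the documents do not support that.
- **Uptake may be high.** The 61% comes from cited background work and is not this trial's forecast. The planning assumption is 90%, where the distortion is small. This stands, so a spurious effect of about half the target (6.1 of 12.8 points) is one corner of the table: 61% uptake with k = 0.7, or about 75% with k = 0.6. The 75% is itself rough, since the section it comes from gives a 6-month inclusion window where VI.C.2 gives 12.
- **Direction is not shown.** No section gives completers' risk. Patients with more experience of coercion might be keener to write a directive, which would reverse the bias. Readmission might block completion or prompt it. This stands: bias in favour of PAD is plausible but not established.
- **Completion in controls is undefined.** Keeping nearly all controls is an inference from the usual-care description. The SAP's words could also be read as excluding a control who drafts a directive. That is fair, but leaving it open is part of the defect.
- **The alternative has weaknesses.** Peer-worker contact may have effects without a written document, which strains the exclusion restriction if exposure means a written PAD only. Exposure counted up to 12 months overlaps the outcome window. A control's self-written directive is not the facilitated intervention. All three stand and shape the fix.

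None of this makes completers and controls a randomised comparison.

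**Conclusion.** The concern holds for the complementary analysis only. As defined, that analysis conditions on a post-randomisation choice in the PAD arm with no counterpart in usual care, and the SAP offers neither a definition of completion nor a method for the selection. Over the assumed range of k, the spurious reduction is small at the planned 90% uptake (at most 2.7 points) and becomes material if uptake falls towards 75% or 61% (up to 6.1 and 8.8 points). These figures rest on an assumed risk ratio, retention of all controls and no true effect. Moderate importance: worth correcting, with no bearing on the sample size or the primary test.

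**What to change.** 1. Replace the per-protocol comparison with a complier-average causal effect on the risk-difference scale: randomisation as the instrument, two-stage estimation, adjustment for site, bootstrap confidence interval.
2. Define exposure identically in both arms from the process indicators already scheduled, and confirm that a completed PAD is captured for controls at 6 and 12 months.
3. Prespecify two exposure definitions, one as the sensitivity analysis for the other: any peer-worker contact or written PAD; and written PAD only.
4. Record the completion date, because a directive can be written after the first involuntary admission in the window, and state how such cases count.
5. State the monotonicity and exclusion assumptions, and say which exposure definition strains the latter.
6. Keep any per-protocol table as descriptive, without a test.

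Cost: SAP wording and possibly one item at existing interviews. The interval is wider and the estimate relies on the stated assumptions. If data collection has ended, the analysis can still be done but should be labelled post hoc; where control uptake was not recorded, vary it over a stated range such as 0 to 3%.
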